**(2) Evaluation Methods**

A. Compare the entire incidence of adverse events that have causal relationship with the SS-PDS use (including control group’s suture) between A+C arm and B+D arm. (significance is judged by p-value 0.05).

B. Compare the incidence of adverse events by type that have causal relationship with the SS-PDS use (including control group’s suture) between A+C arm and B+D arm (significance is judged by p-value 0.05).

C. Compare the entire incidence of grade 3 or above adverse events that have causal relationship with the SS-PDS use (including control group’s suture) between A+C arm and B+D arm (significance is judged by p-value 0.05).

D. Compare the incidence grade 3 or above adverse events by type that have causal relationship with the SS-PDS use (including control group’s suture) between A+C arm and B+D arm (significance is judged by p-value 0.05)

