| Major Exclusion Criteria | 1. Patients with previous or present abdominal incisional hernia.  2. Pregnant patients.  3. Patients receiving external radiation treatment to the pelvis or abdomen.  4. Patients allergic to PDS components.  5. Patient with diseases that affect wound healing including uncontrolled diabetes, autoimmune vasculitis, and hepatocirrhosis.  6. BMI>35  7. Patients are excluded if they have used or are expected to use drugs that may affect wound healing such as bevacizumab. In case where bevacizumab is used, participation is possible if they have a four-week washout period before and after surgery, respectively.  8. Patients who have had an abdominal midline laparotomy for the last 6 months.  9. If patients had surgery for suspected infection. |
| Efficacy Assessment | The efficacy of SS-PDS will be confirmed if 1-year cumulative incidence of incisional hernia in the experimental group is lower than that of the SS-PDS control group (p value 0.05) |
| Safety Assessment | Comparison of prevalence and grade of adverse events between SS-PDS experimental group and control group. |
| Schedule of Visit/Inspection | Baseline: eligibility check  Surgery: fascia closure with SS-PDS or conventional suture, subcutaneous drain insertion, collecting surgery-relevant parameters, pain level survey after surgery  4 weeks after surgery: surgical site infections and wound dehiscence are studied.  1 year after surgery: incisional hernia is judged. |
| Statistical Methods | Comparison of incidence of incisional hernia between SS-PDS experimental group and control group using Chi-square or Fisher’s exact test. |
| Expected Effects and Results | It is expected that the standard surgical method will be changed to fascia closure using barbed suture.  Incidence of incisional hernia is reduced to improve patients’ quality of life and reduce medical costs. |

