**2) Trial Hypothesis and Purpose**

(1) Schema

[figure not shown]

(2) Primary Objective

The purpose of this trial is to verify the hypothesis: ‘In comparison to sutures without barbs, using SS-PDS for abdominal fascia closure on female patients who undergo incisional hernia in midline laparotomy due to gynecological diseases will reduce the cumulative incidence of incisional hernia for 1 year after surgery.’

(3) Secondary Objective

A. Compare the incidence curves of incisional hernia over time between A+B arms and C+D arms (depending on whether SS-PDS is used or not).

B. Compare cumulative incidence and types of surgical site infections up to 4 weeks after surgery between A+B arms and C+D arms (depending on whether SS-PDS is used or not).

C. Compare incidence and cumulative incidence of wound dehiscence at Week 4 after surgery between A+B arms and C+D arms.

D. Compare BPI-K scores that are obtained on Day 2 after surgery between A+B arms and C+D arms (depending on whether SS-PDS is used or not)

E. Compare BPI-K scores that are obtained on Day 4 after surgery between A+B arms and C+D arms (depending on whether SS-PDS is used or not)

F. Compare NRS scores that are collected until Day 4 after surgery between A+B arms and C+D arms (depending on whether SS-PDS is used or not)

G. Compare cumulative incidence of surgical site infections and their types until Week 4 after surgery between A+C arms and B+D arms (depending on whether subcutaneous drain was used or not)

H. Compare incidence and cumulative incidence of wound dehiscence between A+C arms and B+D arms at Week 4 after surgery (depending on whether subcutaneous drain was used or not).

I. Compare incidence of adverse events, their type and relevance excluding incisional hernia, pains, surgical site infections, and wound dehiscence between A+B arms and C+D arms.

J. Create a surgical video of abdominal fascia closure using SS-PDS.

1. **Code Names (or Generic Names of Principal Components) of Investigational Product and Medical Device, Raw Material Quantities, Formulation and etc. (including** **comparator)**

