A. investigators: investigators at each institution can view CRF and check randomization results without a separate approval procedure.

B. study subjects: if investigators see it necessary for medical purposes, they can inform the subjects of the randomization results after approval by the principal investigator.

(8) Interim Analysis

A. Interim analysis for the initial safety review

A) When the 10th subject is allocated to A+B arm and finishes his/her Week 4 visit, an evaluation will be performed on 10 subjects in A+B arm for incidence, types, and grades of surgical site infections, wound dehiscence, and other adverse events.

B) Evaluation results will be reported to IRB. If incidence, types, and grades of adverse events are judged to exceed the usual range, possible measures including trial discontinuation will be considered.

B. Interim analysis for wound dehiscence of subcutaneous drain

A) An evaluation will be performed when the 44th subject of A+C arm and B+D arm, respectively, completes his/her week 4 visit.

B) If wound dehiscence incidence of A+C arm is lower than B+D arm (one-sided p < 0.005), it will be decided that subcutaneous drain insertion reduces wound dehiscence and further randomization will be stopped. That is to say that subcutaneous drain will be inserted to all subject from then.

1. **Investigational Product Dosage, Application/Administration Methods, Combination Therapy, and Reasons for Comparator (as applicable)**

(1) SS-PDS arm (fascia closure using SS-PDS)

A. Instructions

A) STRATAFIX Symmetric PDS Plus, suture size: 1/0, suture length: 45cm, needle size: 40mm (CT needle) (Ethicon, Somerville, NJ, USA)

B) Running suture will be used as recommended by the manufacturer and stated in previous studies [PMID: 28603661] (<https://www.youtube.com/watch?v=PTYtYvSaGMg>, <https://youtu.be/TPyulS4fQgQ>)

C) Peritoneum closure should be performed. If peritoneum closure is impossible due to peritoneotomy, it may not be performed.

D) For fascia closure, stiches will be made 5-8 mm apart including 5-8 mm thick tissues on both sides of the incision surface.

E) It is allowed to make additional stiches for fascia closure with a few interrupted sutures using PDS or other sutures based on the investigator’s judgment.

F) Suture length is recommended to be 4 times longer than the skin incision. That is, if the skin incision is 20cm, it is recommended to use 80cm or longer suture for closure.

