**(1) Causality Evaluation**

A. Investigators will determine that there is or there is no causal relationship with the SS-PDS use (including control group’s suture). If it is difficult for the investigator to make a judgment, it will be judged to have a causal relationship.

B. Causality will not be evaluated for the use of subcutaneous drain.

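### The only thresholded tests for residual adverse events count events that investigators, who may know the suture, attribute to it; once the group labels are corrected, attribution can bias the suture comparison

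*Protocol*

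**What the plan says.** **The four tests.** In the protocol's safety section (Evaluation Standards, Methods and Reporting of Safety Including Side Effects), (2) Evaluation Methods sets out four comparisons: all events, events by type, events of grade 3 or above, and grade 3 or above by type. Item A begins "Compare the entire incidence of adverse events that have causal relationship with the SS-PDS use", and B-D carry the same restriction. Each has the rule "significance is judged by p-value 0.05". The printed groups are "between A+C arm and B+D arm. (significance is judged by p-value 0.05".

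**Who attributes.** Under (1) Causality Evaluation, investigators decide for either suture whether an event is related. For doubtful cases, "If it is difficult for the investigator to make a judgment, it will be judged to have a causal relationship". Causality is not assessed for the drain.

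**What they may know.** Under Control Group Setting and Randomization, the institution learns the allocation by phone just before fascia closure (item 5). Afterwards, "investigators at each institution can view CRF and check randomization results without a separate approval procedure" (item 7). Under (3) Reporting Methods, the expedited-reporting category is defined by the SS-PDS arm together with causality.

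**What is promised elsewhere.** The overview's safety assessment reads "Comparison of prevalence and grade of adverse events between SS-PDS experimental group and control group". Secondary objective I reads "Compare incidence of adverse events, their type and relevance excluding incisional hernia, pains, surgical site infections, and wound dehiscence between A+B arms and C+D arms". The last row of the table under Efficacy Evaluation Standards, Evaluation Methods plans a summary and comparison of the remaining adverse events without an attribution filter. That row names no test, threshold or groups.

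**The concern.** An adverse event enters tests A-D only if it occurs and an investigator then blames the suture. Randomisation protects the first step. It does not protect the second if the investigator knows which suture was used.

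There is a reason to expect different thresholds for blame. Under Benefits for and Risks to Subjects, the protocol says there is little clinical experience with SS-PDS for this closure and lists potential risks for it, while the comparator is described as standard practice. Novelty could raise attribution in the SS-PDS arm. Reluctance to blame the study device could lower it. So in a suture comparison, equal event rates could give a significant result, or a real difference could disappear, through attribution alone. The threshold also sits on a narrower outcome than the overview and objective I describe.

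**Working it through.** **1. Which groups the tests compare.** The secondary objectives define A+C against B+D as the drain contrast: "between A+C arms and B+D arms (depending on whether subcutaneous drain was used or not". Objective I uses A+B against C+D for adverse events, and the overview names the suture groups in words. The groups printed in A-D therefore do not match the stated safety objective. This matters for the bias as well, because A+C and B+D each contain both sutures.

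**2. Sample size.** The protocol gives no figure for the safety tests. The only N is 87 per pooled arm (0.13 versus 0.03, one-sided 0.05, power 0.8, dropout 0.06). The arcsine formula reproduces it: h = 2·asin(√0.13) − 2·asin(√0.03) = 0.390, n = 2(1.645 + 0.842)²/h² = 82, and 82 × 1.06 = 87. After 6% dropout, 87 × 0.94 = 82 remain. I use 82 per arm for false positives, with 87 as a check.

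**3. Model.** Rate of patients with a related event = event rate × attribution share. The test is a two-sided chi-square at 0.05; the protocol does not state the sides for A-D, so two-sided is assumed. Rejection probabilities come from exact enumeration of two binomials. Event rates and attribution shares are assumptions.

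**4. False positives on A+B versus C+D, equal true event rates.**

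| Event rate, both arms | Attribution | Related rates | 82 per arm | 87 per arm |
|---|---|---|---|---|
| 30% | 20% vs 30% | 0.06 vs 0.09 | 10.3% | 11.0% |
| 30% | 20% vs 40% | 0.06 vs 0.12 | 26.4% | 28.1% |
| 50% | 20% vs 30% | 0.10 vs 0.15 | 15.9% | 16.7% |
| 50% | 20% vs 40% | 0.10 vs 0.20 | 43.4% | 45.4% |
| 30% or 50% | equal, 20% | 0.06 or 0.10 in both arms | 4.2% or 4.9% | 4.3% or 5.0% |

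**5. A hidden difference, 87 per arm.** Take a true 40% versus 20%.
- All events counted: power 83%.
- Half of the events attributed in each arm (0.20 vs 0.10): power 45%.
- Attribution 30% in the higher-rate arm and 60% in the other (0.12 vs 0.12): rejection 5%, the null rate.

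**6. The contrast as printed.** I simulated the four cells (44, 43, 43, 44) with related rates that depend on the suture, from 0.16 vs 0.08 to 0.40 vs 0.20. A+C versus B+D rejects in 4% to 5% of trials throughout, because each side has the same mix of sutures. For the same reason, this contrast does not test a real suture difference.

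**The case against.** Several points on the other side stand.

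- **Harm is largely tested without the filter.** A reader might infer that the randomised comparison of harm is lost. The protocol does not support that. The risks it names for SS-PDS are hernia, surgical site infection, dehiscence and pain. All of these are compared by suture at 0.05 in the efficacy table with no causality filter. The point concerns the remaining events, many of which the protocol expects from surgery and cancer treatment.
- **An unfiltered comparison of the remaining events is planned.** That its test and threshold are not named may be left to an analysis plan and is not the fault here. The fault is that the threshold the protocol does fix sits on the filtered outcome.
- **Relatedness is part of objective I.** Objective I includes the relevance of events, so reporting related events is legitimate. It does not make them the only tested set.
- **The printed tests do not show the bias.** A reader might infer that A-D as they stand would yield false suture signals. They would not, because attribution by suture cancels in A+C versus B+D. The bias appears when the labels are corrected.
- **Knowledge of the suture is permitted but not certain.** Allocation is kept off the medical records. The hernia row says investigators are blinded until Year 1, and the infection row says they are not reminded of allocation. Nothing says that the surgeon in theatre judges causality. Against this, the adverse-event row has no blinding statement, CRF access is open, and the expedited-reporting category depends on the arm.
- **Doubtful cases count as related for both sutures.** This limits under-attribution. Deciding that a case is doubtful is still a judgement that may be made with the arm known.

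**Conclusion.** The point holds for adverse events other than hernia, pain, surgical site infection and dehiscence. For these, every comparison with a stated threshold depends on attribution by investigators who may know the suture, although the overview and objective I are not limited to related events.

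The bias is conditional on reconciling the groups with A+B versus C+D. Under the assumed event rates of 30% and 50%, at 82 per arm, false positives run from 10% (attribution 20% versus 30%) to 43% (20% versus 40%), against 4% to 5% when attribution is equal. Detection of a true 40% versus 20% difference can fall from 83% to 5% at 87 per arm. These figures show what a given attribution gap would do. The protocol gives no basis for the size or direction of the gap. The primary endpoint is unaffected. The change is worth making because correcting only the labels would expose the suture comparison to this bias.

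**What to change.** Make two changes together in the safety section, (2) Evaluation Methods:

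1. Correct the groups in A-D to A+B versus C+D, in line with the overview and objective I.
2. Apply the four tests to all adverse events (any; by type; grade 3 or above; grade 3 or above by type) whatever the attributed cause, in line with the last row of the efficacy table. Report suture-related events by arm descriptively, which still serves the relevance part of objective I.

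The cost is protocol wording. The observation table already has all adverse events collected and graded without a causality restriction. The downside is some noise from unrelated surgical and cancer-treatment events; the descriptive table of related events beside the tests helps the reader to judge it.

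### All four comparisons of suture-related adverse events are set between A+C and B+D, the drain contrast, contradicting the protocol's own adverse-event objective

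*Protocol*

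**What the plan says.** The arm labels are fixed under Secondary Objective. Objectives G and H make their comparisons "between A+C arms and B+D arms (depending on whether subcutaneous drain was used or not"), while objectives A, B and D to F tie A+B versus C+D to whether SS-PDS is used. The table under Efficacy Evaluation Standards, Evaluation Methods uses the labels the same way.

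The safety section then departs from this. Under (2) Evaluation Methods, item A concerns "adverse events that have causal relationship with the SS-PDS use (including control group’s suture) between A+C arm and B+D arm". Item B repeats the comparison by type. Item C begins "Compare the entire incidence of grade 3 or above adverse events that have causal relationship with the SS-PDS use" and item D "Compare the incidence grade 3 or above adverse events by type that have causal relationship with the SS-PDS use"; both also end with A+C against B+D. Each item adds that "significance is judged by p-value 0.05".

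Two other places state the adverse-event comparison:

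- Secondary objective I reads: "Compare incidence of adverse events, their type and relevance excluding incisional hernia, pains, surgical site infections, and wound dehiscence between A+B arms and C+D arms".
- Overview, Safety Assessment: "Comparison of prevalence and grade of adverse events between SS-PDS experimental group and control group".

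Three further places bear on it. (1) Causality Evaluation, item B, says that causality is not assessed for the drain. The adverse-event row of the evaluation table names neither arms nor a test. Data Analysis and Statistical Analysis Methods, item (1), refers the reader back to the evaluation table and to this safety section for the between-group analyses.

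**The concern.** Items A to D count events attributed to the suture, in either suture group, and then split them by drain. That answers no question the protocol asks. The inclusion of events attributed to the control suture makes sense only if one suture is to be compared with the other.

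These four items are also the only adverse-event comparisons for which the protocol fixes both the arms and a significance level. Followed literally, they would set SS-PDS patients against SS-PDS patients and control-suture patients against control-suture patients, in equal mixture. An absence of difference in suture-related or grade 3 and higher events would then be the expected result whether or not SS-PDS raises their frequency. Under Benefits for and Risks to Subjects the protocol concedes that clinical experience with SS-PDS in abdominal fascia closure is limited, so the comparison is worth having in a form that can inform.

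**Working it through.** **Inputs from the protocol.** Allocation is 1:1 for the suture and 1:1 for the drain (Control Group Setting and Randomization). There are 87 patients in each of A+B and C+D, 174 in all (Target Sample Size). The significance level is 0.05.

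**Assumptions.** The protocol gives no adverse-event rates, no sidedness and no named test for these items. Used here: a range of illustrative rates, a two-sided level, the uncorrected chi-square test, and no suture-by-drain interaction.

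**The plan's own figure.** No figure is stated for the safety tests. The 87 per group reproduces with the arcsine formula: h = 2·asin(√0.13) − 2·asin(√0.03) = 0.3896; n = 2(1.645 + 0.842)²/h² = 81.5; 81.5/0.94 = 86.7, rounded up to 87. The labelling error does not affect it.

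**Expected difference.** Arm A is SS-PDS with drain, B SS-PDS without, C control suture with drain, D control suture without. Let suture-related events occur at rate e with SS-PDS and c with the control suture. With equal arms:

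- A+C: (e + c)/2
- B+D: (c + e)/2, so the difference is 0
- A+B minus C+D: e − c

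For e = 20% and c = 5%, A+C and B+D are both 12.5%, while A+B and C+D differ by 15 points.

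**Rejection rates.** Simulation of 200,000 trials per row, arms of 44, 43, 43 and 44:

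| Control vs SS-PDS (assumed) | A+C vs B+D, as written | A+B vs C+D |
|---|---|---|
| 5% vs 5% | 4.2% | 4.2% |
| 5% vs 20% | 4.4% | 88.0% |
| 10% vs 30% | 4.3% | 92.4% |
| 20% vs 40% | 4.6% | 83.2% |
| 10% vs 40% | 3.9% | 99.8% |
| 2% vs 50% | 2.1% | 100% |

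**Check of the last column by formula, 5% vs 20%.** Pooled rate 0.125. Null standard error √(2 × 0.125 × 0.875/87) = 0.0501. Alternative standard error √((0.20 × 0.80 + 0.05 × 0.95)/87) = 0.0488. Power = Φ((0.15 − 1.96 × 0.0501)/0.0488) = 85.5%, close to the simulated 88.0%.

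**Why the middle column falls below 5%.** The test uses the pooled variance p(1 − p), but each side is a fixed half-and-half mixture with the smaller variance [e(1 − e) + c(1 − c)]/2. For 5% vs 20% these are 0.1094 and 0.1038, so the effective critical value is 1.96 × √(0.1094/0.1038) = 2.01, a two-sided rejection rate of 4.4%. For 2% vs 50% they are 0.1924 and 0.1348, giving 2.34 and 1.9%. A larger suture effect makes the written test slightly less likely to reject.

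**Two departures from the simple case.**

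- *Early stop of drain randomization.* With arms of 65, 22, 65 and 22 and rates of 10% vs 30%, A+C vs B+D rejects in 4.2% of runs. The cancellation persists as long as the suture stays 1:1 within each drain group.
- *Interaction.* If harm occurs only with SS-PDS and drain together (40% in A, 10% elsewhere, assumed), A+C is (40 + 10)/2 = 25% against 10% in B+D, and the written contrast rejects in 76.9% of runs. The result would be read as a drain effect.

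**The case against.** The strongest reply is that this is a label slip and not a chosen analysis. Objective I and the Overview both name the suture contrast, and the drain is excluded from causality assessment, so a careful analyst would see what was meant. That is probably right about intent, and it is why the point is an internal contradiction. It does not settle the matter. The same contrast appears in all four items, the adverse-event row of the evaluation table names no arms, and the statistical section sends the reader back to these items. An unseen analysis plan is no answer either, because the protocol states the contrast wrongly and does not leave it open.

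A reader might also infer that the trial cannot detect any harm from SS-PDS. The protocol does not support that. The potential SS-PDS risks it lists are hernia, surgical site infection, wound dehiscence and pain, and the evaluation table tests each of them between A+B and C+D. The early safety review examines the first ten A+B patients, and expedited reporting is tied to the SS-PDS arm. These last two are not comparative tests, but the error does not touch them.

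Nor does every suture effect cancel whatever the truth: the cancellation is in expectation and needs no interaction between suture and drain. Finally, no data are lost. Adverse events and their relation to the suture are collected in all arms, so the intended comparison can still be computed.

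**Conclusion.** Wrong as written. Items A to D of (2) Evaluation Methods place every comparison of suture-related adverse events on the drain factor, against objective I and the Overview. Under 1:1 allocation on both factors and no interaction, the expected difference due to the suture is zero. The tests then reject at or below the nominal level, about 2% to 5% in simulation, where A+B versus C+D would have over 80% power for assumed differences of 15 points or more. The cancellation follows from the design; the power figures rest on illustrative rates, a two-sided 0.05 level and the chi-square test. The consequence is limited to these four tests. The primary endpoint, the sample size, randomization, both interim analyses, and the comparisons of hernia, infection, dehiscence and pain are unaffected.

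**What to change.** In items A, B, C and D of (2) Evaluation Methods, replace A+C and B+D with A+B and C+D. Name the same arms in the adverse-event row of the table under Efficacy Evaluation Standards, Evaluation Methods, so that all statements of the adverse-event comparison agree. Make the change before the between-arm comparison of adverse events is run, so that the contrast is not chosen after results are known.

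The cost is a short text amendment. It needs no additional patients, data or visits and no change to randomization.

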**3) Subcutaneous Drainage Experimental Group**

Jackson-Pratt drain, 7 Fr (Manufacturer to be determined)

**4) Subcutaneous Drainage Control Group :** N/A

1. **Subject Eligibility and Exclusion Criteria, Target Sample Size and Calculation Rationale**
2. **Inclusion Criteria**

(1) Female patients planning to undergo elective midline laparotomy for gynecological diseases.

(2) Over 18 years old.

(3) ECOG performance status 0 - 2

1. **Exclusion Criteria**

(1) Patients with previous or present abdominal incisional hernia.

(2) Pregnant patients.

(3) Patients receiving external radiation treatment to the pelvis or abdomen.

(4) Patients allergic to PDS components.

(5) Patient with diseases that affect wound healing including uncontrolled diabetes, autoimmune vasculitis, and hepatocirrhosis.

(6) BMI>35

(7) Patients are excluded if they have used or are expected to use drugs that may affect wound healing such as bevacizumab. In case where bevacizumab is used, participation is possible if they have a four-week washout period before and after surgery, respectively.

(8) Patients who have had an abdominal midline laparotomy for the last 6 months.

(9) If patients had surgery for suspected infection.

1. **Target Sample Size and Calculation Rationale**

(1) Previous study results were referenced to assume 1-year cumulative incidence of incisional hernia as 0.13 in SS-PDS control group (C+D arm) [PMID: 26188742].

(2) No previous studies have investigated the incidence of incisional hernia after using barbed suture for abdominal fascia closure. Given that there are cases of very low incisional hernia incidence such as 1-2% in previous studies using conventional closure methods, 1-year cumulative incidence of incisional hernia in SS-PDS experimental group (A+B arm) is estimated to be 0.03.

(3) Alpha 0.05 (one-sided), power 0.8, drop-out rate 0.06, each arm (A+B vs C+D): 87 patients

(4) Therefore, the target sample size is 174.

1. **Recruitment Plan**

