| Compare wound dehiscence incidence at Week 4 between A+C arm and B+D arm (depending on whether subcutaneous drain is inserted or not) | Incidence of wound dehiscence of A+C arm will be compared with that of B+D arm using chi-square or Fisher's exact test. P value 0.05 will be used to determine significance. | Patients who undergo surgery and complete week 4 visit |
| Incidence, types, grades and relevance of adverse events excluding incisional hernia, pains, surgical site infections, and wound dehiscence. | Incidence, type and grade of adverse events except incisional hernia, pain, SSI, wound dehiscence will be summarized using appropriate metrics. They will be compared using appropriate statistical methods. | Patients who undergo surgery. |

1. **Distinctions from conventional treatments and studies**

(1) Using barbed suture for abdominal fascial closure falls within the range of treatments approved by US FDA and Korea MFDS.

(2) Using barbed suture for abdominal fascial closure has a possibility to reduce potential incisional hernia.

(3) There is a lack of systematical studies for abdominal fascial closures using barbed suture.

1. **Benefits for and Risks to Subjects**

(1) Predictable side effects/risks and countermeasures

A. Regardless of predictable side effects/risks – causality,

this trial targets female patients who undergo midline laparotomy. Therefore, various adverse events involved with surgery may be observed. Also, a considerable number of subjects are expected to be diagnosed as and treated for malignant tumor, and adverse events may be observed in this regard.

A) Blood and lymphatic system disorders: anemia, febrile neutropenia, hemolysis, leukocytosis

B) Cardiac disorders: palpitations, sinus bradycardia

C) Ear and labyrinth disorders: vertigo

D) Eye disorders: Blurred vision, conjunctivitis, dry eye

E) Gastrointestinal disorders: abdominal distension, abdominal pain, anal pain, ascites, bloating, constipation, diarrhea, dry mouth, dyspepsia, enterocolitis, fecal incontinence, flatulence, ileus, intra-abdominal hemorrhage, nausea, vomiting

F) General disorders and administration site conditions: chills, edema face, edema limb, fatigue, fever, infusion related reaction, infusion site extravasation, irritability, localized edema, non-cardiac chest pain, pain

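### Suture-related adverse events are compared by a 0.05 significance verdict with no effect estimate or interval, which at 87 per arm says little about harm in rare event types

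*Protocol*

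**What the plan says.** The section on evaluation and reporting of safety, (2) Evaluation Methods, sets out four comparisons of adverse events judged causally related to the suture, in either suture group: all events (A), events by type (B), all grade 3 or above (C), and grade 3 or above by type (D). Each carries the same criterion, "significance is judged by p-value 0.05"; with its contrast, item A reads "between A+C arm and B+D arm. (significance is judged by p-value 0.05". The section names no test, sidedness, effect measure or interval.

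Three other places bear on the same analysis:

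- Overview, Safety Assessment: "Comparison of prevalence and grade of adverse events between SS-PDS experimental group and control group".
- Secondary Objective I compares adverse events "excluding incisional hernia, pains, surgical site infections, and wound dehiscence between A+B arms and C+D arms".
- The last row of the efficacy evaluation table says that adverse events "will be summarized using appropriate metrics. They will be compared using appropriate statistical methods".

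The section on data analysis and statistical methods refers the reader back to the efficacy and safety evaluation sections for the between-group comparisons. Items A to D are therefore the protocol's stated criterion, not a placeholder. The sample size rationale rests on hernia alone: "Alpha 0.05 (one-sided), power 0.8, drop-out rate 0.06, each arm (A+B vs C+D): 87 patients".

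**The concern.** A significance verdict is a poor summary of safety when events are few. Items B and D apply it to single event types, including severe ones, where counts will be smallest, in a trial sized for a ten-point difference in hernia (13% against 3%). Non-significance is then the likely result whether or not SS-PDS does harm.

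The protocol acknowledges, under the risks of barbed suture, that clinical experience with SS-PDS in abdominal fascia is limited, and adds that no increase in complications is expected. A row of p-values above 0.05, with no interval beside them, could easily be taken to confirm that expectation. What is at stake is how much the final safety comparison can tell the reader about the device under test.

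**Working it through.** **Inputs.** 87 per suture group, 1:1 allocation, hernia rates 0.13 and 0.03, one-sided alpha 0.05, power 0.80 and drop-out 0.06 (sample size rationale). Safety threshold 0.05 (Evaluation Methods, A to D). The protocol gives no adverse event rates, so those below are assumptions.

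**1. The plan's own figure.** The arcsine formula is n = 2[(z₀.₉₅ + z₀.₈₀)/h]², with h = 2·asin√0.13 − 2·asin√0.03 = 0.738 − 0.348 = 0.390. This gives n = 81.5 per arm, and 81.5/0.94 = 86.7, rounded up to 87. The stated size is reproduced, and it depends on hernia rates only.

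**2. Smallest one-sided splits that reach 0.05.** For k events in one arm and none in the other, two-sided Fisher p = 2·C(87,k)/C(174,k). For k = 5 this is 2 × 0.02946 = 0.0589. At 87 per arm:

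| Split | Fisher, two-sided | Fisher, one-sided | Chi-square, uncorrected | Chi-square, Yates |
|---|---|---|---|---|
| 3 vs 0 | 0.246 | 0.123 | 0.081 | 0.244 |
| 4 vs 0 | 0.121 | 0.060 | 0.043 | 0.129 |
| 5 vs 0 | 0.059 | 0.029 | 0.023 | 0.070 |
| 6 vs 0 | 0.029 | 0.014 | 0.013 | 0.038 |

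With 81 or 82 per arm, roughly the number left after drop-out, 5 vs 0 is still p=0.059 by two-sided Fisher.

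**3. Power under assumed rates.** Power is the sum of Bin(a; 87, p₁)·Bin(b; 87, p₂) over all pairs (a, b) with two-sided p<0.05.

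| Assumed rates | Fisher | Chi-square, uncorrected |
|---|---|---|
| 2% vs 6% | 13% | 24% |
| 5% vs 10% | 16% | 23% |

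**4. What an interval would show.** Newcombe 95% intervals for the risk difference:

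- 6/87 − 2/87 = 4.6 points, interval −2.2 to +12.1, two-sided Fisher p=0.28. The p-value alone hides that an excess of about 12 points is not excluded.
- 5/87 − 0/87 = 5.7 points, interval +0.4 to +12.8, while two-sided Fisher gives 0.059.
- 0/87 − 0/87: upper limit about +4.2 points.

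**5. The contrast as written.** Secondary Objectives G and H use the same grouping, "between A+C arms and B+D arms (depending on whether subcutaneous drain was used or not", so A+C against B+D is the drain factor. Each side holds about half of the SS-PDS patients. Suppose ten related events occur, all in SS-PDS patients. Split at random between A+C and B+D, they reach p<0.05 only for 0–10, 1–9, 9–1 or 10–0: (1 + 10 + 10 + 1)/1024 = 2.1% of the time. Compared by suture group, the same ten events are 10 vs 0, p=0.0015.

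**The case against.** The strongest reply has four parts.

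- **Test not fixed.** Items A to D name neither test nor sidedness, and the efficacy table allows chi-square or Fisher for binary outcomes. A reader might infer from the two-sided Fisher figures that the rule cannot flag an event type with five or fewer cases. The document does not support that without a condition: one-sided Fisher flags 5 vs 0 (p=0.029) and uncorrected chi-square flags 4 vs 0 (p=0.043). This stands, although expected counts of 2 to 2.5 per cell would usually lead to Fisher. The low power does not depend on the choice, since chi-square also misses an assumed tripling from 2% about three times in four.
- **Other safeguards.** A reader might also infer that safety is judged by p-values alone. It is not. The protocol plans a review of the first ten A+B subjects, gives the principal investigator discretion to stop, requires reporting of serious unexpected related events, collects other events yearly, and summarises adverse events. This too stands. However, these are oversight and description, and none commits to a final between-arm estimate with its uncertainty.
- **No stated misreading.** Nowhere does the protocol say that a non-significant result means equal safety. That is correct; the risk lies in interpretation.
- **Common limitation and SAP detail.** Any trial of this size has low power for rare events, pooled items A and C will have larger counts than items B and D, and table layout belongs in an SAP. All fair. But the protocol did not leave the criterion open: it fixed a significance verdict, and an interval at least shows how much remains unknown.

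**Conclusion.** The point holds in limited form. Items A to D set p=0.05 as the criterion for comparing suture-related adverse events and plan no effect estimate or interval. At 87 per arm that criterion has little ability to show harm in rare types: 5 vs 0 gives p=0.059 by two-sided Fisher, and detection of an assumed rise from 2% to 6% is 13% (Fisher) to 24% (chi-square). A non-significant result would be weak evidence about safety.

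The power figures rest on assumed event rates, on 87 per arm, and on the SS-PDS against control contrast that Objective I and the Overview call for. Items A to D as written compare by drain, and no interval from that contrast would inform on the suture. The arms must therefore be reconciled first, but correcting them alone would leave the significance-only criterion in place.

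This is a worthwhile correction to analysis and reporting. It does not show that harm would go unnoticed during the trial.

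**What to change.** In the safety section, (2) Evaluation Methods, items A to D:

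1. Change the contrast to A+B against C+D, in agreement with Secondary Objective I and the Safety Assessment in the Overview.
2. Replace the significance criterion with n/N per arm and the SS-PDS minus control risk difference with a two-sided 95% confidence interval (for example Newcombe), for all events, each type, grade 3 or above, and grade 3 or above by type.
3. Treat any p-value as descriptive, and state that p above 0.05 is not evidence of equal safety.
4. List every suture-related grade 3 or above event individually.

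Do not add a rule that draws the safety conclusion from the upper confidence limit. No margin is set, and even no events in either arm leaves an upper limit of about 4.2 points.

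The cost is a protocol or analysis-plan wording change and a table format, with no extra data or patients. The downside is that safety no longer has a simple significant or not-significant verdict.
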